### Data management and analysis

#### Data management

A data management plan was developed to specify all procedures relating to the handling of trial data. Management of data for the masked outcome data will be handled by the Clinical Trials Unit at the Armauer Hanssen Research Institute (AHRI) with support from the trial statisticians. Data will be doubled entered from the Patient Report Forms into an electronic Case Report Form. Trial data with unmasking potential (process data and data pertaining to adverse events) will be handled by the Butajira mental health research office following the same standardised operating procedures as for the Clinical Trials Unit. Data cleaning based on frequency distributions and logic checks will follow standard procedures with reference to source documents as required.

#### Data analysis approach

Data analysis will follow a detailed statistical analysis plan that specifies all planned analyses. Data analysis will take place using Stata Version 13 (Stata Corporation, College Station, Texas, USA) under the direction of the trial statisticians. All analyses will be masked to study arm until the analysis is finalized and approved by all investigators. Descriptive analyses will include frequency distributions and measures of central tendency and dispersion, as appropriate, with 95 % confidence intervals. Bivariable comparisons will employ χ^2^, Fisher’s exact, Student’s t- or rank-sum tests, as appropriate. All statistical tests will be one-sided at α = 0.05, as we are testing a hypothesis of non-inferiority and not superiority or equivalence.

Analysis will be by intention-to-treat, that is, on the basis of the group to which the participant is allocated randomly at the beginning of the trial. Intention-to-treat has the potential to lead to false acceptance of the hypothesis of non-inferiority in the presence of a true difference if there is a large cross-over from the primary care to the psychiatric nurse service [60]. Therefore, the intention-to-treat analysis will be presented together with the percentage of participants who deviate from the protocol in the following ways: (1) cross-over protocol deviation which is indicated by the percentage who attend for more than two consecutive visits at the service they were not randomised to receive, unless they were referred to that service, and (2) disengagement from care protocol deviation, which is the percentage who miss more than 50 % of their scheduled health facility appointments (not attending within 2 weeks of the appointment date). Per protocol analyses will also be conducted, and the findings presented as a sensitivity analysis. Account will be taken of clustering at the level of the health facility.

Analysis will be carried out on the complete data set at 12 and 18 months. For the primary outcome time-point of 12 months, it would not be appropriate to carry forward the last observation to replace missing data as this would have taken place at the baseline of the study and could, therefore, increase the chance of non-inferiority even in the presence of a difference between the allocated services.

If more than 15 % of the primary outcome scores are missing, we will conduct multiple imputation analysis (including age, sex, baseline symptom severity and substance use disorder) in the model and present this as an exploratory analysis alongside the analysis on the complete dataset.

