### The need for trials of task-sharing interventions for mental health care

Despite the potential advantages of task-sharing mental health care, little is known about how different aspects of the care needed by people with SMDs can be safely and effectively transferred to the PHC setting in a rural, low-income country setting such as Ethiopia. In a recent review of task-sharing approaches to health care in LMICs, evidence was offered that task sharing can improve the productive efficiency of services (that is, the greatest amount of care at a given quality and a given cost), although challenges regarding quality, safety and sustainability were also identified [20]. Most of the identified evaluations of task sharing were in the fields of surgery, obstetrics and HIV care, and few employed randomised, controlled trial designs. With respect to mental health care in particular, little is known about the acceptability of task sharing to service users or PHC workers [24] or the feasibility and sustainability of such a model [25, 26]. Uncertainty also exists as to whether stigma will be greater or lesser in a separate psychiatric clinic that is further from the place of residence compared to an integrated service that is in the person’s locality. The paucity of clinical trials of interventions for SMD in Africa has been highlighted, concluding that there is a pressing need for high-quality evidence from pragmatic trials with adequate follow-up periods [27]. In a consensus exercise conducted to set priorities for global mental health, the integration of mental health care into primary care was within the top five issues to be addressed to improve scale-up and impact of mental health care [28]. The TaSCS trial, therefore, addresses an important evidence gap and has the potential to inform policy initiatives to scale-up mental health care in the African region and beyond.

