### Rationale for a non-inferiority trial

In this trial, we propose to investigate the non-inferiority of a task-sharing model of mental health care in PHC compared to the established alternative service model within Ethiopia: a less accessible (more centralised), but more specialist, psychiatric nurse-led model of care. The psychiatric nurse-led model of care has been demonstrated to be acceptable and associated with improved clinical outcomes for people with SMD engaged in the service in this sample in Butajira, Ethiopia, thus making this an appropriate comparison model [2]. Task-sharing mental health care in PHC in Ethiopia is expected to allow more mental health care to be provided for the same cost compared to expanding specialist mental health care and is, therefore, of critical importance in addressing the high treatment gap. However, the important policy question for Ethiopia, and other low-income countries, is to establish whether or not the new task-sharing model for mental health care in PHC is good enough to meet the needs of people with SMD. At present, no evidence exists to inform this policy question. We will therefore conduct a non-inferiority trial in order to evaluate whether or not task sharing is at least no worse than specialist mental health care across a range of outcomes.

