The non-inferiority margin for the primary outcome needs to be defined in relation the minimal clinically important difference (MCID) [53]. Previous studies have defined clinically significant change in score on the BPRS-E in different ways. Using a statistical approach, the ‘reliable change index’ [54] for change in BPRS-E score from beginning to end of an in-patient admission in persons with SMD equated to 18 points [55]. However, change in symptoms in a person with acute psychosis receiving in-patient care is likely to be larger than the MCID and not applicable to the out-patient sample of people with SMD to be included within this sample. In a study looking at change in symptoms in response to a psychological intervention for an out-patient sample of people with chronically symptomatic schizophrenia, a mean change of 7.9 points on the BPRS-E was considered clinically important [49]. A mean change of 7.9 points equates to a standardised effect size of around 0.50, which we take to be the MCID. In line with recommendations for non-inferiority trials, the non-inferiority margin for this trial will be 75 % of the presumed MCID, that is, a six-point difference in mean BPRS-E scores between arms of the trial [53, 56]. A six-point difference on the BPRS-E equates to a standardised effect size of 0.4.

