#### Secondary outcomes

See Table 2.

A wide range of secondary outcomes are being assessed in view of the importance of exploring the full range of possible harms when conducting a non-inferiority trial. The secondary outcomes are functional impairment, relapse of SMD, service use costs, satisfaction with mental health care, nutritional status, service use for physical health conditions, disengagement from care, non-adherence with medication, experience of side effects, perceived stigma, experience of being restrained, quality of care and adverse events. Caregiver outcomes are perceived stigma, family burden, time burden and opportunity costs of care giving.

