### Sample size calculation

The following formula was used to calculate the required sample size (n):$$ n={2}^{*}{\left[\sigma /\Delta \right]}^2\;{\left({Z}_{\alpha }+{Z}_{\beta}\right)}^2, $$

where delta = non-inferiority margin (mean BPRS-E scores of six points), sigma is the standard deviation of the BPRS-E score (estimated standard deviation of 15 [57]), Z_alpha_ is the standardised mean difference for the probability of type 1 error (alpha = 0.05) and Z_beta_ is the standardised mean difference for the probability of type 2 error (beta =0.1 (that is, power of 0.9). Therefore, a sample size of 107 persons per arm of the trial (that is, a total of 214) is required [58]. No published studies from Ethiopia are available to guide us in our estimation of the intra-cluster correlation (ICC) for study subjects receiving treatment from a specific health centre. We therefore estimate the ICC to be 0.01, which is the median ICC from a review of 31 cluster-based interventions in PHC [59]. Given that there are 13 health centres within the three districts covered by the Ethiopia TaSCS trial, the design effect will be 1 + (n-1)*ICC (where n = number of subjects per cluster). Therefore, the design effect = 1 + (17–1)*0.01 = 1.16. Assuming a worst-case scenario of 30 % loss to follow-up, the required sample size = 214 * 1.30 * 1.16 = 323 participants. For equal numbers in each arm of the trial, the total sample size will be 324 (n = 162 in each arm).

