#### Analysis of primary outcome

The analysis for the primary outcome will be carried out by AHRI in order to ensure masking of the treatment group. The primary outcome measure (change in BPRS-E score) will be analysed using linear regression adjusting for baseline symptom severity. Statistical tests will be one-sided, reflecting our interest in testing the hypothesis that task-shared care is non-inferior. The validity of regression assumptions will be checked using residual plots. For the purpose of safety monitoring, the Phase 1 primary outcome at 12 months will be analysed as an interim analysis. For the purpose of hypothesis-testing for the main trial, Phase 1 and Phase 2 primary outcomes at 12 months will be combined. Both crude and adjusted (for baseline symptom severity, age and sex) effect sizes will be presented for the primary analysis. Exploratory analysis of the non-inferiority of the new intervention in the Phase 1 and Phase 2 participants will be carried out separately.

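### The article makes every test one-sided on non-inferiority grounds, but that reason covers only BPRS-E, the one outcome for which it states a margin

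*Protocol article*

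**What the plan says.** The rule stands under Data analysis approach, directly after a list of bivariable tests, and makes no exception: "All statistical tests will be one-sided" at 0.05, on the ground that the hypothesis is one of non-inferiority rather than superiority or equivalence. Analysis of primary outcome repeats one-sidedness for BPRS-E alone: "Statistical tests will be one-sided, reflecting our interest in testing the hypothesis that task-shared care is non-inferior". The earlier sentence is therefore not just the primary rule in other words.

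The only margin in the article is six BPRS-E points (Hypothesis, Primary outcome, Sample size calculation). The Primary outcome section puts it on a standardised scale: "A six-point difference on the BPRS-E equates to a standardised effect size of 0.4".

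Elsewhere the article says what the other outcomes are for:
- Rationale for a non-inferiority trial: to evaluate whether task sharing is "at least no worse than specialist mental health care across a range of outcomes".
- Secondary outcomes: the wide range is justified by the "importance of exploring the full range of possible harms when conducting a non-inferiority trial".
- The need for trials of task-sharing interventions for mental health care: "Uncertainty also exists as to whether stigma will be greater or lesser" in a separate clinic than in a local integrated service. Perceived stigma is a secondary outcome and a caregiver outcome in Table 2.
- The Background, on the WHO model: placing mental health care in primary care may improve physical health care. Service use for physical conditions is a secondary outcome in Table 2.

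Analysis of secondary outcomes refers the planned approach to Additional file 3, which is not at hand.

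**The concern.** A one-sided test at 0.05 answers a non-inferiority question only if its null hypothesis is placed at a margin. Where no margin exists, the null is zero difference, and the test asks only whether one arm is worse (or better) in a direction chosen in advance. The article does not name that direction for any outcome except BPRS-E.

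No single direction serves the stated aims. If the tests point at harm, a reduction in stigma or a gain in physical health care cannot reach significance, however large. If they point at benefit, the harms that justify the wide outcome list cannot. In the harm direction, a non-significant result is also easily mistaken for evidence that task sharing is no worse on that outcome. At stake are the conclusions on secondary, caregiver and adverse-event outcomes, which matter for a policy decision on scaling up. The primary conclusion is not at stake.

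**Working it through.** **1. Does one-sided 0.05 fit the primary outcome?** Inputs from Sample size calculation: margin 6, SD 15, alpha 0.05, power 0.90.

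n per arm = 2 × (15/6)² × (1.645 + 1.2816)² = 107.05. The article states 107 per arm, 214 in total. With the article's own inflation, 214 × 1.30 × 1.16 = 322.7, which it gives as 323 and rounds to 324. At one-sided 0.025 the formula gives 131.3, or 132 per arm, which does not match. The primary design is therefore consistently one-sided at 0.05.

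**2. What does the same rule do without a margin?** Take a continuous outcome in SD units, 107 per arm, a normal approximation and no design effect. The standard error of the difference is √(2/107) = 0.1367 SD. Let d be the true difference, positive for harm, with the one-sided test pointed at harm.

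- One-sided 0.05: P(significant) = 1 − Φ(1.645 − d/0.1367).
- Two-sided 0.05: P(significant) = 1 − Φ(1.960 − d/0.1367) + Φ(−1.960 − d/0.1367).

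| True difference | One-sided, pointed at harm | Two-sided |
|---|---|---|
| Benefit 0.4 SD | below 0.00001 | 0.83 |
| Benefit 0.3 SD | 0.00006 | 0.59 |
| Benefit 0.2 SD | 0.0009 | 0.31 |
| Harm 0.2 SD | 0.43 | 0.31 |
| Harm 0.3 SD | 0.71 | 0.59 |
| Harm 0.4 SD | 0.90 | 0.83 |

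If the test points at benefit instead, the table is mirrored and the near-zero entries fall on harms.

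**3. What does a non-significant result show?** With harm as the tested direction, the chance of missing a true harm is 1 − 0.43 = 57% at 0.2 SD, 29% at 0.3 SD, and 10% at 0.4 SD, which is the size of the primary margin. Non-significance is thus common under real harms and cannot stand for being no worse.

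**4. What would an interval show?** The half-width of a two-sided 95% confidence interval is 1.960 × 0.1367 = 0.27 SD. This tells the reader directly which harms and benefits remain compatible with the data.

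**The case against.** The strongest reply is that the detail may lie elsewhere. The article points to Additional file 3 and to a detailed analysis plan. If margins or directions are set there for particular outcomes, one-sided tests suit those outcomes. This stands, so the point is limited to what the article states. It does not rescue the sentence itself, which covers every test, including stigma, whose direction the article calls open. The 95% confidence intervals mentioned under Data analysis approach do not clearly help either, since they are attached to descriptive analyses.

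Several stronger readings are tempting and not supported:
- A reader might infer that the tests can never show task sharing to be no worse. A benefit-pointed test that rejects would show superiority and hence no worse; its fault is that it cannot see harm.
- A reader might infer that two-sided tests would reduce the number of false signals. At 0.05 they carry the same 5% total per outcome, split between the two directions.
- A reader might infer that cost savings could not be shown. The Economic analysis section estimates cost differences with their uncertainty and does not rest on one-sided tests.
- A reader might infer that the rule is undefined for the listed χ² test. The article names no multi-category outcome for it, and a one-sided version exists for two-by-two tables.
- A reader might infer that harms would go unnoticed during the trial. The DSMB reviews adverse events by arm for inferiority of either arm, with early and twice-yearly reporting.
- A reader might infer that the authors plan to read non-significance as no worse. The article never says so; the risk follows from combining its rationale with the tests it prescribes.

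**Conclusion.** The sentence is wrong as written. Its justification applies to BPRS-E only, yet it governs every test, and the article's own statements on stigma, physical health care and harms cannot be served by one direction. At 107 per arm, a 0.3 SD effect in the untested direction would be flagged with probability about 0.00006 rather than 0.59. In the tested direction, a 0.2 SD harm would be non-significant 57% of the time.

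These figures assume a continuous outcome, a normal approximation, the plan's 107 per arm, no design effect and a null of zero. They illustrate size; the argument about direction does not depend on them. The conclusion is conditional on no margin being set in the files not shown. The primary test and its sample size are sound on this point.

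**What to change.** Replace the blanket sentence with three statements:
- One-sided alpha 0.05 applies to the BPRS-E non-inferiority test against the six-point margin only.
- Secondary, caregiver and adverse-event comparisons are reported as between-arm estimates with two-sided 95% confidence intervals and two-sided tests.
- No non-inferiority claim is made for an outcome unless a margin for it is prespecified in Additional file 3 or the analysis plan.

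The edit is short and leaves the sample size of 324 as it is. The price is power in whichever single direction would have been tested: 0.90 to 0.83 for a 0.4 SD effect and 0.71 to 0.59 for 0.3 SD. In return, effects of the same size in the other direction become detectable with the same 0.83 and 0.59.

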**Methods/Design:**

A randomised, controlled, non-inferiority trial will be carried out in a predominantly rural area of Ethiopia. A sample of 324 people with SMD (diagnoses of schizophrenia, schizoaffective disorder, bipolar disorder or major depressive disorder) with an ongoing need for mental health care will be recruited from 1) participants in a population-based cohort study and 2) people attending a psychiatric nurse-led out-patient clinic. The intervention is a task-sharing model of locally delivered mental health care for people with SMD integrated into PHC delivered over 18 months. Participants in the active control arm will receive the established and effective model of specialist mental health care delivered by psychiatric nurses at an out-patient clinic within a centrally located general hospital. The hypothesis is that people with SMD who receive mental health care integrated into PHC will have a non-inferior clinical outcome, defined as a mean symptom score on the Brief Psychiatric Rating Scale, expanded version, of no more than six points higher, compared to participants who receive the psychiatric nurse-led service, after 12 months. The primary outcome is change in symptom severity. Secondary outcomes are functional status, relapse, service use costs, service satisfaction, drop-out and medication adherence, nutritional status, physical health care, quality of care, medication side effects, stigma, adverse events and cost-effectiveness. Sustainability and cost-effectiveness will be further evaluated at 18 months. Randomisation will be stratified by health centre catchment area using random permuted blocks. The outcome assessors and investigators will be masked to allocation status.

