#### Butajira hospital psychiatric out-patient clinic

In Butajira, the general hospital has a psychiatric out-patient clinic run by psychiatric nurses. At present this clinic is the only mental health care available within the districts covered by the TaSCS trial, as is the case in most of Ethiopia [37]. Since completion of the Butajira SMD cohort recruitment, additional people with SMD living in the Butajira SMD/TaSCS recruitment area have sought care from this clinic because they are (1) incident cases, (2) missed cases from the original recruitment, or (3) they have migrated into the area. If the TaSCS trial is unable to recruit a sufficient sample size from the Butajira SMD cohort, consecutive attendees at the Butajira hospital psychiatric clinic will be screened for eligibility.

Recruitment into the trial will be divided into two phases. In Phase 1, only people with SMD who are clinically stable will be recruited. Three months after beginning recruitment, the Data Safety and Monitoring Board (DSMB) will review adverse events, including non-engagement with the service, disengagement from care and evidence of potentially dangerous prescribing, before Phase 2 recruitment is permitted. In Phase 2, people with SMD who have more complex needs or who are clinically unstable will be recruited.

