### Masking

Outcome assessors and trial investigators will be masked to the intervention allocation of participants, but it is not possible for trial participants and clinicians involved in delivering the intervention service to be masked. To minimise the possibility of unmasking of outcome assessors, 1) outcome assessments will be carried out by project-employed mental health professionals and lay interviewers in a location that is independent of and geographically separated from the health service; 2) the outcome assessors will not work in the trial districts; 3) when patients and caregivers are registered for their follow-up assessments, they will be instructed not to tell the interviewer where they are receiving mental health care; 4) selected trial clinical assessments will be observed by non-project psychiatrists to ensure that ratings are being conducted without bias; and 5) at the end of each follow-up assessment, the assessor will be asked whether they have become unmasked to patient allocation group during the course of the assessment. This information will be used to conduct a sensitivity analysis to investigate any evidence of bias. Data analysis for the primary outcome will be carried out by an independent organization, and those involved in data analysis will be masked to the intervention status of the participant.

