### Interventions

#### Intervention arm

The intervention is a task sharing model of mental health care for people with SMD integrated into PHC, as recommended by the WHO in the mental health Gap Action Programme (mhGAP) [21] and endorsed by the Ethiopian Federal Ministry of Health [16]. Adaptation of the task-sharing model for the study setting was informed by extensive formative work and community consultation in the study site [40] and from findings arising from a sister project implementing integrated mental health care in a neighbouring district [43, 44].

In the TaSCS intervention, PHC-based health centre nurses and health officers will be trained to deliver the mhGAP packages of mental health care, supported by community-based health extension workers. The training and supervision requirements are summarised in Table 1. As all trial participants have an existing care plan used by project psychiatric unit staff, this will be transferred to PHC when a patient has been randomised to a PHC site. A minimum of monthly, facility-based follow-ups will be stipulated during the initial phase, and thereafter, 3-monthly follow-ups, although contacts can be more frequent depending on patient need. The current outreach by project workers will be replaced by outreach by health extension workers, who are required to make house-to-house visits every 3 months, as part of their health promotion and illness prevention responsibilities. Psychiatric nurse-led mental health support will be provided to the PHC health officers and nurses through (1) supervision including case reviews, discussion of difficult cases, developing supportive relationships with the primary health care provider and trouble-shooting; (2) emergency consultation with project psychiatric nurses; and (3) referral for a second opinion or for a period of follow-up by the specialist team in Butajira psychiatric unit, as per mhGAP guidelines. Psychiatric nurses can in turn consult project psychiatrists. The roles of the PHC workers in the task shared model are summarised in Additional file 2.

**Table 1 Tab1:** Task sharing intervention for the Task Sharing for the Care of Severe Mental Disorders in a Low-income Country (TaSCS) trial

Recipients	Intervention	
	Training	Ongoing support and structures

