#### Active comparison arm

The active comparison sample for the TaSCS trial is a psychiatric nurse-led, centralised model of out-patient specialist mental health care augmented by community outreach by lay workers as part of the Butajira SMD study. There are 57 psychiatric nurse-led units across Ethiopia providing the lion’s share of specialist mental health care in the country [37]. Psychiatric nurse-led clinics constitute the only model of mental health care available in rural areas in Ethiopia. The comparison arm of the TaSCS trial can be considered to be an enhanced version of specialist mental health care, in that community outreach is provided. Evaluation of the longitudinal illness course of patients in the Butajira SMD study showed improved outcomes for those who engaged with the service compared to those who did not engage [2].

The Butajira hospital psychiatric nurses are able to prescribe psychotropic medication (including depot antipsychotic medication), monitor and intervene against side effects, diagnose co-morbid psychiatric conditions and provide simple psychosocial interventions. Follow up will be arranged on the basis of need, but at least a face-to-face assessment every three months. Consultation with project psychiatrists or referral for in-patient psychiatric care (in Addis Ababa) will be as indicated.

The psychiatric nurses will receive 2 days of refresher training in order to familiarise them with the WHO’s evidence-based guidelines for management of mental disorders (mhGAP-IG). They will also receive refresher training on the management of SMD in pregnant and breastfeeding women.

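### Clustering on health facility does not fit a control arm treated at one clinic: with facility-clustered robust errors, false non-inferiority would be about 10–12% instead of 5%

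*Protocol article*

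**What the plan says.** Under Data analysis approach, the protocol article states: "Account will be taken of clustering at the level of the health facility". It gives no estimator there and leaves the detail to a separate analysis plan. Analysis of primary outcome names a linear regression with baseline severity as covariate and no cluster term. Tests are one-sided at 0.05.

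The two arms are organised differently:

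- **Control arm.** Care is "delivered by psychiatric nurses at an out-patient clinic within a centrally located general hospital". Of that clinic the article says: "At present this clinic is the only mental health care available within the districts covered by the TaSCS trial". Active comparison arm describes a "psychiatric nurse-led, centralised model of out-patient specialist mental health care".
- **Intervention arm.** "PHC-based health centre nurses and health officers will be trained to deliver the mhGAP packages of mental health care", so these patients are spread over the health centres.

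Randomisation is individual, with health-centre catchment area as the stratum, so each stratum contains both arms.

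Sample size calculation introduces the ICC for participants treated at a given health centre, then says "the design effect will be 1 + (n-1)*ICC (where n = number of subjects per cluster", with 17 per cluster, 13 health centres and ICC 0.01. The resulting 1.16 multiplies the total for both arms.

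Under Masking, "those involved in data analysis will be masked to the intervention status of the participant".

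**The concern.** Read as written, the cluster is the facility where a patient is treated. That gives about 13 clusters in one arm and one in the other. A single control cluster carries no information on variation between control facilities, and any effect of that clinic cannot be separated from the arm effect. Routine ways of allowing for clustering then fail in opposite directions:

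- **Cluster-robust errors.** Residuals in a linear regression with an arm term sum to zero within each arm. The control cluster's contribution to the variance of the arm effect is therefore zero, or close to zero once baseline is a covariate. About half the true variance disappears.
- **A facility random intercept in both arms.** The model charges the arm comparison with the full variance of one unreplicated control intercept, and the standard error is inflated.

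The first error matters more. It narrows the confidence bound that decides the trial, and so favours declaring the new service non-inferior. The planned model is a linear regression in Stata, where clustered errors are a routine option, so this is a realistic way to carry out the sentence.

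**Working it through.** **Inputs from the protocol article** (Sample size calculation; one-sidedness from Data analysis approach): margin 6, SD 15, one-sided α 0.05, power 0.90, ICC 0.01, 13 health centres, 30% loss, 162 randomised per arm.

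**Assumptions not in the documents:** ICC 0.05 as an alternative; a baseline–outcome correlation of 0.5 where stated; 12 centres as an alternative to 13 (the results barely change).

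**1. The plan's own figure.** n = 2 × (15/6)² × (1.6449 + 1.2816)² = 107.05, so 107 per arm and 214 in total. 214/13 = 16.5, taken as 17. Design effect = 1 + 16 × 0.01 = 1.16. 214 × 1.30 × 1.16 = 322.7, so 323, then 324. The stated size reproduces.

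**2. Cluster size.** Dividing 214 by 13 spreads control patients over health centres that do not treat them. For the intervention arm alone, 107/13 = 8.2 per centre. Its design effect is 1 + 7.2 × 0.01 = 1.07, and the average over both arms is (1.07 + 1)/2 ≈ 1.04.

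**3. Standard error of the difference, without baseline adjustment.** Analysed per arm: 162 × 0.70 ≈ 113. 225/113 = 1.991 and 113/13 = 8.7 per centre, so the intervention-arm design effect is 1.077.

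- Reference (clustering in the intervention arm only): √(1.991 × 1.077 + 1.991) = √4.135 = 2.03.
- Cluster-robust by treating facility (control contribution lost): √(1.991 × 1.077) = 1.46, which is 28% too small. One-sided error at a true difference of 6: 1 − Φ(1.645 × 1.46/2.03) ≈ 0.12.
- Facility random intercept in both arms, ICC treated as known: between-facility variance 0.01 × 225 = 2.25, within 222.75. Variance = 2.25/13 + 222.75/113 + 2.25 + 222.75/113 = 6.365, so SE 2.52, which is 24% too large.

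**4. Simulation at a true difference of 6** (4,000 trials, 113 per arm, 13 centres, ICC 0.01, a baseline covariate unrelated to outcome). The empirical SD of the estimate was 2.06.

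| Method | Mean SE | One-sided error |
|---|---|---|
| Robust, treating facility | 1.44 | 0.108 (t, 13 df) to 0.124 (normal) |
| Ordinary regression SE | 2.00 | 0.055 |
| Robust, catchment area | 2.00 | 0.051 (t, 12 df) |

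**5. With an assumed baseline correlation of 0.5** (6,000 trials per setting, 12–13 centres). The facility-clustered SE averaged 1.25–1.26 against a true 1.77–1.78, about 29% too small. The error was 11.2–11.5% at ICC 0.01 and 9.5–10.1% at ICC 0.05. Clustering on catchment gave 4.8–4.9% and 5.1%.

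**6. Random intercept in both arms.** In 300 simulated trials without a baseline covariate, the one-sided error was about 0.03. This route does not raise false claims. With baseline correlation 0.5 the SE was recomputed at 2.18–2.32, against the same 1.77–1.78.

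**The case against.** The strongest reply is that the protocol fixes no standard-error method. The clustering sentence is general and an unseen analysis plan may carry it out validly. A random health-centre effect in the intervention arm only is itself a way of allowing for facility clustering. The one model that is named, ordinary linear regression, holds close to 5% at the planned ICC. The sample size section, by putting both arms into 13 clusters, could be read as meaning catchment areas. All of this stands, and it makes the finding conditional. It does not remove it: the stated cluster level is the facility, the ICC is introduced for patients treated at a health centre, and a literal implementation in the planned software gives the wrong bound.

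A reader might infer four stronger things that the documents do not support:

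- *The standard error is wrong whatever the method.* Catchment clustering and a partially nested model both come out close to correct.
- *The analysts' masking is broken.* No text says masked analysts receive facility codes, and Data management keeps data that could reveal allocation with a separate office. What is fair to say is that a facility code holding about half the sample would reveal arm if it were used.
- *Power falls to 77%.* That figure comes from SE 2.52, which omits the planned baseline adjustment. With correlation 0.5, power is about 83–87% against about 96% for the correct model. The loss depends on both the ICC and the correlation.
- *Nesting biases the comparison.* Centralised against local care is the randomised contrast. Having one control clinic limits generalisation and does not bias that contrast.

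**Conclusion.** The point holds in conditional form. Treating facility is nested in arm with one control cluster, so the stated level of clustering does not suit this design. If it is applied through cluster-robust errors in the planned regression, the standard error is about 25–30% too small at ICC 0.01, and the chance of a false non-inferiority claim at the margin is about 10–12% rather than 5%. The error stays near 10% at an assumed ICC of 0.05. A random facility intercept in both arms instead inflates the standard error and loses power. These sizes rest on 113 analysed per arm, SD 15 and 12–13 centres of about equal size.

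The design effect is inconsistent with the control arm's organisation, but in the safe direction: 1.16 against about 1.04 at ICC 0.01. That margin is specific to the planned ICC. At 0.05 the intervention-only average would be (1 + 7.23 × 0.05 + 1)/2 ≈ 1.18. The correction does not call for more patients.

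**What to change.** 1. Replace the clustering sentence under Data analysis approach. Include health-centre catchment area, the randomisation stratum, in the primary model. Then either cluster on catchment area, or add a random health-centre effect for intervention-arm patients only. In both cases use small-sample degrees of freedom, because there are only about 13 clusters.
2. State that the masked analysis uses a catchment code, which occurs in both arms and so does not reveal allocation, rather than a treating-facility code.
3. Under Sample size calculation, restate the design effect as applying to the intervention arm only: about 8 per centre, 1.07 in that arm, about 1.04 overall. Note that 1.16 was conservative at ICC 0.01 and that the target of 324 stands as far as this point is concerned.

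The cost is wording and standard model code, with no added patients, visits or data, since catchment area is already recorded for randomisation. The change should be made before allocation is unmasked.
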